## Abstract

**Background:**

The SCHEMA trial evaluates whether interpersonal art psychotherapy reduces the frequency/severity of aggressive incidents or patient distress associated with psychiatric symptoms, compared to usual care.

**Objective:**

To describe the statistical and health economic analysis plan.

**Methods:**

A multicentre, two-arm, parallel-group, single blind individually randomised controlled trial with 150 adults within NHS secure care who have borderline to mild/moderate intellectual disability. The primary outcome is the frequency/severity of aggressive behaviour, measured on the Modified Overt Aggression Scale (MOAS) 19 weeks post-randomisation, analysed using a linear mixed-effect model, adjusted for baseline MOAS and stratification by gender and psychosis diagnosis. Changes in aggressive behaviour will be evaluated using weekly MOAS scores between 19 and 38 weeks. Patient distress relating to psychiatric symptoms will be assessed using the Brief Symptom Inventory Positive Symptom Distress Index across baseline, 19, and 38 weeks. Health-related quality-of-life will be assessed using self- and proxy-reported EQ-5D three-level (EQ-5D-3L) and Recovering Quality of Life 10-item measures, the latter to estimate the ReQoL Utility Index, across baseline, 19, and 38 weeks. The self-reported EQ-5D-3L is collected using an adapted version for people with intellectual disabilities. Resource-use is collected based on secure care records, to estimate intervention and healthcare costs over 19 and 38 weeks. HRQoL and cost data will inform cost-effectiveness based on the incremental cost per quality-adjusted life year over 38 weeks.

**Discussion:**

This paper details the planned analyses and discusses recruitment challenges, sample size implications, and effect size assumptions. The plan was developed prior to database lock and unblinding to minimise analytical bias.

**Trial registration:**

ISRCTN, ISRCTN57406593. Registered on 18/01/2023.

**Supplementary Information:**

The online version contains supplementary material available at 10.1186/s13063-025-08934-3.

## Background

Aggression and violence are a cause of major problems in psychiatric and secure inpatient care [1]. An international review indicated that patients in secure care settings are likely to be more violent than those in other types of psychiatric units, with 69% of assaults against NHS staff in England occurring in mental health or intellectual disability (ID) settings [2]. It has also been suggested that patients being treated in a secure care intellectual disability ward are more likely to stay in high and/or medium secure care for longer, compared to patients on other types of secure mental health wards [3]. There is reasonable evidence of the pharmacological treatment in violence reduction where people have mental illness in forensic settings [4], and this treatment may also be likely to have a positive impact on violence in people with ID and comorbid mental illness. However, there is limited evidence for the effective use of psychotropic medication as well as non-medicinal psychotherapies for the treatment of challenging behavior in people with ID. Therefore, the development of effective interventions for people in secure care with ID and borderline intellectual functioning (BIF) is a priority.

Art psychotherapy (art therapy) is used in some NHS services to help children, young people, and adults with mental health difficulties [5, 6]. A systematic review of the clinical efficacy of art therapy among people with non-psychotic mental health disorders concluded that art therapy appeared to have statistically significant positive effects compared with usual care [7]. National practice-based guidelines have been developed for art therapy with people who have an ID [8]. Initial findings from a systematic review reported better outcomes for individual therapy compared with group-based interventions [9]. In a systematic review and meta-analysis of art therapy in forensic settings (secure care), mechanisms and positive effects of arts therapies were indicated to reduce risk and increase protective factors in individuals in forensic institutions [10].

Interpersonal Art Psychotherapy has been developed in the UK as a manualised intervention delivered by a trained art psychotherapist registered with the Health and Care Professions Council (HCPC) [11]. The SCHEMA trial aims to determine whether interpersonal art psychotherapy can reduce the frequency and severity of aggressive incidents and/or patient self-reported distress associated with psychiatric symptoms, compared to usual care. The study population includes adults within secure care who have borderline to mild/moderate ID [12].

A protocol paper describing the design of SCHEMA has previously been published [12]. This paper describes the detailed statistical and health economic analysis plan (SHEAP) for SCHEMA and specifies the statistical and health economic models for evaluation of the primary and secondary outcomes, including the covariates to be included in the adjusted analyses, and has been prepared in accordance with the published guidelines on the content of statistical analysis plans [13] (see Appendix D). In accordance with good clinical practice and to avoid outcome reporting bias [14], the SHEAP was developed before the database was locked and data analysis was initiated.

### Trial objectives

#### Primary objective

To assess the effectiveness of interpersonal art psychotherapy (compared to usual care) in reducing the frequency and severity of aggressive behaviour in adults in secure care [12].

#### Secondary objectives

To determine if interpersonal art psychotherapy is cost-effective compared to usual care.To explore patient characteristics and psychotherapeutic processes/mechanisms within interpersonal art psychotherapy that are influential to treatment.To explore the longitudinal changes in aggressive behaviour after receiving art psychotherapy.To evaluate changes in patient distress related to psychiatric symptoms.

## Methods

### Trial design

Full details of the SCHEMA trial design, setting, intervention, outcomes, and ethical approvals have been published in the protocol [12]. However, we provide a summary here as follows. The trial is a multicentre, two-arm, parallel-group, single-blind, individually randomised controlled trial (RCT) of effectiveness, comparing manualised interpersonal art psychotherapy to usual care. The RCT is being conducted in 8 NHS Trusts with secure care facilities and aims to recruit 150 participants (75 per trial arm). The total trial duration is 43 months with 20 months of recruitment. The end of the trial is defined as the last participant’s last visit [12].

The intervention arm is scheduled to receive 12 (1 h each) individual interpersonal art psychotherapy sessions, delivered by a trained HCPC registered art psychotherapist, plus usual care. Participants can receive up to 3 additional sessions throughout the trial for more personalised support, adjusting for the participant’s specific communication or therapeutic needs. The sessions cover the following 7 components: (1) personal goals, (2) coping responses and self-management, (3) relationships, (4) life events, (5) interpersonal themes, (6) imagined future and (7) final review. Participants will be considered as having completed the intervention if they complete at least 5 out of the 7 components listed above.

The control arm is scheduled to receive usual care, and participants are assessed and treated by specialist professionals. The multi-disciplinary team includes psychiatrists, clinical and forensic psychologists, mental health and ID nursing staff, and Allied Health Professionals. The team uses the Care Programme Approach to coordinate and plan participant care, including risk assessments, recovery-focused care and/or positive behaviour support [15]. Participants also have access to psychotherapy/psycho-educational work, specific offence-related treatment and pharmacotherapy treatment. Participants in the control arm are offered the art psychotherapy intervention at the end of their participation in the trial.

### Ethical approval

This protocol and related trial documents were reviewed by the London-City & East Research Ethics Committee and received full approval on 13/01/2023 (REC ID: 23/LO/0026; IRAS project ID: 319,325). Informed consent was obtained from all participants prior to being entered into the trial [12].

This is a low-risk trial of non-investigational medicinal product (NIMP); therefore, a Data Safety Monitoring Board was not required. This was discussed and approved by the Trial Steering Committee (TSC). The TSC review all safety data and have met at least annually. The TSC comprises members independent of the trial, serving as chair, statistician, expert therapist, and a public member, all of whom have signed the remit and conditions outlined in the TSC Charter [12].

### Randomisation

Participants were randomly allocated to receive either art psychotherapy plus usual care (UC) as the intervention arm, or UC with delayed art psychotherapy as the control arm. Participants were allocated to the intervention and control arm in a 1:1 ratio using randomly permuted blocks of 2, 4 and 6 created in Stata (version 17). This concealed allocation and minimised the predictability of the next allocation at the end of each block. Randomisation was stratified by sex and diagnosis of psychosis to achieve balance of baseline characteristics in the two groups.

The final randomisation list was generated by the senior statistician independently, keeping the trial statistician blind to the randomisation list. Randomisation took place online through the REDCap SCHEMA database and was available 24 h a day. Treatment allocations were automatically generated once the participant’s baseline data had been entered. As this is a single blind trial, the trial statistician, health economist and research support staff completing the primary outcome assessment are kept blind to allocation. For the statistical analysis, all data cleaning, manipulation, and analysis will be carried out by the trial statistician who will be kept blind to the arms allocation.

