### Adherence and protocol deviations

#### Adherence

Participants’ adherence to art psychotherapy is recorded as the proportion of randomised participants completing the intervention (completion of 5 out of 7 components of art psychotherapy). Intervention fidelity is recorded as the proportion of therapists adhering to the treatment manual. A therapist’s adherence to art psychotherapy is monitored during supervision sessions. Audio recorded sessions are optional and a random sample of 3 timepoints for 3 participants across 9 therapists (27% of sessions) will be blind rated using the interpersonal art psychotherapy treatment fidelity checklist, incorporating tested methods for assessing treatment fidelity (see Appendix A). Where participants do not consent to having intervention sessions audio-recorded, the number of components covered and sessions attended will be recorded as part of the week-19 follow-up. Descriptive statistics on participant adherence and intervention fidelity will be presented in a table, overall and by trial arm.

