### Analysis population

The analysis will be performed on an ITT basis; therefore, all participants who are randomised will be included in the analysis. However, if missing outcome data do not meet any appropriate assumptions such as considering the outcome was missing because the intervention was not effective, the analysis will be limited to a complete-case analysis. All protocol violations including participants who have not completed at least 5 components out of the 7 components of art psychotherapy will be considered, and we will conduct a per-protocol analysis where applicable. In addition, we will conduct a sensitivity analysis for missing outcome observations and other important variables such as psychometrics.

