### Descriptive statistics: baseline and other time-points

Baseline characteristics will be summarised by trial arm using appropriate descriptive statistics.

Categorical data will be summarised by numbers and percentages. Continuous data will be summarised by means (SD) if data are normally distributed and medians (IQR) if data are skewed. Minimum and maximum values will also be presented for continuous data. Summary statistics will be visualised using appropriate graphical plots, including bar graphs, histograms, and boxplots. Baseline and outcome measures will be summarised overall and by trial arm. Tests of statistical significance will not be undertaken for baseline characteristics; rather, the clinical importance of any imbalance will be noted in the trial report. Baseline data will also be summarised for those who completed follow-up compared to those lost to follow-up (i.e. no data at weeks 19 and 38) to assess possible dropout bias.

For the economic analyses, descriptive statistics will focus on the EQ-5D-3L and ReQoL-10 item scores and utility scores, QALYs, resource-use and costs across all resource-use items. Intervention resource-use and costs will also be presented separately to the downstream resource-use and cost descriptive statistics, i.e. the resource-use and cost associated with interpersonal art psychotherapy. All descriptive statistics will be provided as stratified by trial-arm, at/up to each data collection time-point (i.e. at baseline, at/up to 19 weeks and 38 weeks), and across all time-points (i.e. over 38 weeks) as appropriate.

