### Analysis of primary outcome

The aim of the primary analysis is to examine the effectiveness of art psychotherapy in reducing the frequency and severity of aggressive incidences compared to usual care, as measured by the change in MOAS score from baseline to week 19 post-randomisation. The distribution of the MOAS scores will be assessed graphically using histograms and the mean (SD) or median [IQR] of the change in score from baseline to week 19 will be tabulated overall and by trial arm (art psychotherapy versus usual care). The change of primary outcome from baseline to week 19 will be assessed graphically using a scatter plot.

The primary outcome analysis will be performed on an ITT basis. Initially, we will use a linear mixed-effect regression model [27, 28], with the week-19 MOAS score as the dependent variable and the randomisation group as the independent variable, adjusted for the baseline MOAS score, random effect of the variable indexing strata based on gender and diagnosis of psychosis. In addition, we anticipate potential clustering in the intervention arm due to therapists. We will examine this by the ICC from the linear mixed-effect model and if there is a considerable amount of heterogeneity in the primary outcome associated with therapists, we will adjust the effect estimate for the partial clustering due to therapists. For this, both partially homoscedastic and heteroscedastic regression models will be explored, and we will report the results as appropriate. The homoscedastic model assumes between-cluster variability is only present in the intervention arm and the individual level variation is the same in both arms. The heteroscedastic model assumes between-cluster variability is only present in the intervention arm but allows different individual level variation in intervention and control arms [29, 30]. From the initial model(s), we will present the estimated difference in MOAS score at week-19 for the intervention group compared to the control group with 95% CI.

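### The trial statistician is said to do all cleaning and analysis blind, but several planned analyses use data that exist only in the therapy arm, so the claim holds at most up to the initial primary model

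*Protocol article*

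**What the plan says.** The Randomisation section states that "the trial statistician, health economist and research support staff completing the primary outcome assessment are kept blind to allocation". It then says of the statistical analysis that "all data cleaning, manipulation, and analysis will be carried out by the trial statistician who will be kept blind to the arms allocation". No stage or analysis is exempted, and no second, unblinded analyst is mentioned.

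The Trial design section states that "Participants in the control arm are offered the art psychotherapy intervention at the end of their participation in the trial".

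Other sections call for data on therapy received:

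- Adherence: where audio recording is declined, "the number of components covered and sessions attended will be recorded as part of the week-19 follow-up". Also, "Descriptive statistics on participant adherence and intervention fidelity will be presented in a table, overall and by trial arm".
- Analysis population: "participants who have not completed at least 5 components out of the 7 components of art psychotherapy will be considered", with a per-protocol analysis where applicable.
- Analysis of primary outcome: the therapist ICC is examined and, if heterogeneity is considerable, "we will adjust the effect estimate for the partial clustering due to therapists".
- Analysis of secondary outcomes: the mixed models for EQ-5D-3L, ReQoL-10 and BSI PSDI carry a therapist random effect, without condition.
- Descriptive statistics: "Intervention resource-use and costs will also be presented separately to the downstream resource-use and cost descriptive statistics", with all descriptive results split by arm.
- Subgroup analyses: reliable change is analysed in therapy completers.

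**The concern.** A masked arm label (A or B) protects an analyst only while nothing else in the file tells the arms apart. During trial participation only one arm has sessions, components, a therapist and an intervention cost. An analyst who uses any of these fields knows which label is therapy.

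This matters because the plan defers several choices until data are seen:

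- restriction to complete cases, depending on why outcomes are missing (Analysis population);
- the homoscedastic or heteroscedastic therapist model (Analysis of primary outcome);
- transformation, a non-parametric method or dichotomising (Alternative methods if distributional assumptions not met);
- whether to impute (Sensitivity analyses).

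A blind analyst is the natural safeguard for such choices. A report that repeats the Randomisation section as written would claim that safeguard for analyses where it cannot operate.

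**Working it through.** No sample size, power or error rate is involved, so the check sets the blinding statement against the fields that each analysis needs.

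**Step 1: which fields are specific to one arm.** Controls are offered therapy only after their own participation ends. In-trial therapist, session, component and intervention-cost fields therefore belong to the therapy arm. The Withdrawal/follow-up section adds two more that name the arm: withdrawal from art therapy, and withdrawal from the control group's waiting list.

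**Step 2: what each analysis needs.**

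| Analysis | Fields beyond outcome, baseline and strata | Status in the plan | Can the arm code stay masked? |
|---|---|---|---|
| Initial model of week-19 MOAS | coded arm | unconditional | yes |
| Repeated measures ANCOVA of weekly MOAS | coded arm | planned, exploratory | yes |
| Therapist ICC for the primary outcome | therapist | unconditional | no |
| Partially clustered primary models | therapist, and which arm has therapists | if heterogeneity is considerable | no |
| Mixed models for EQ-5D-3L, ReQoL-10, BSI PSDI | therapist | unconditional | no |
| Adherence and fidelity table by arm | components | unconditional | no |
| Per-protocol analysis | components (at least 5 of 7) | where applicable | no |
| Reliable change in completers | components | planned, exploratory | no |
| Intervention resource use and costs by arm | intervention cost | unconditional | no |

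Of these nine, two can be run with the arm masked and seven cannot. Two of the seven are conditional (the partially clustered models and the per-protocol analysis), which leaves 7 − 2 = 5 that the plan carries out in any case.

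**Step 3: does an A/B code rescue the statement?** No. One participant in coded arm A with an in-trial therapist or a non-zero in-trial session count shows that A is therapy and B is control. A therapy participant who attended no sessions is not identified by the count, but is identified through the code. The partially clustered models go further: they place between-therapist variance in the intervention arm only, so they cannot be specified without knowing which label that is. The heteroscedastic version also gives each arm its own individual-level variance.

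**Step 4: the health economist.** Intervention cost is non-zero in one arm, and the Economic evaluation section forms the ICER as intervention against control. Whoever attaches intervention costs to participants knows the arm.

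**The case against.** The strongest reply is about timing. Nothing in the article puts therapy fields in the statistician's file during cleaning. The Analysis of primary outcome section sets an order: first a model with group, baseline MOAS and strata, which needs no therapy field, and only then the therapist question. A reader might infer that the code is open as soon as cleaning starts; the article does not support that. Blinding through cleaning and the initial model is feasible, and this part of the reply stands.

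Second, an article condenses. Masked exports and the order of unblinding may be set out in the full protocol or a data management plan, and the Abstract mentions unblinding as an event. That the article gives no date or person for it is therefore no fault. The reply does not remove the contradiction, though: the Randomisation section makes a positive statement about all analysis, and other sections of the same article require analyses for which it cannot be true.

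Third, a reader might infer that the protection claimed in the Abstract is lost. It is not. That sentence concerns when the plan was written, and Trial status bears it out: approval on 04/02/25, with last follow-up expected on 12/04/2025. Whatever the plan fixes stays fixed, and the Conclusion promises to report deviations.

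Fourth, a reader might infer that allocation is exposed for all 150 participants. That is not established. 150 is a target that the Discussion expects may be missed. Early-recruited controls may also have had therapy after leaving the trial but before database lock, so identification rests on in-trial fields.

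Fifth, the case on the health economist is thinner. The statement about doing all the work blind names only the trial statistician, and the costing text assigns no one.

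**Conclusion.** The blinding statement in the Randomisation section is too wide. It can hold for outcome cleaning and for analyses on a coded arm with therapy fields withheld, including the initial primary model. It cannot hold for the therapist ICC check, therapist-clustered models, adherence table, per-protocol and completer analyses, or intervention costs.

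The size is qualitative: seven of the nine analyses set out above, five of them unconditional. The contradiction does not itself show bias in the treatment estimate, no figure in the plan changes, and blinding of the staff who rate the MOAS is untouched. What is weakened is the safeguard for choices that the plan leaves open.

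Two assumptions are made: that the trial statistician performs the therapist, adherence and per-protocol analyses, as the Randomisation section implies, and that the health economist does the costing, which the article does not state.

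**What to change.** - Reword the Randomisation section so that the trial statistician is blind until the decisions on cleaning, missing data, and the primary outcome's scale and model are signed and dated.
- Until that sign-off, have the senior statistician, who generated the randomisation list, supply a file with outcomes, baseline data, strata and a masked arm code. Therapist, session, component, therapy-withdrawal and intervention-cost fields are held back.
- Fix in advance the rule for choosing between the homoscedastic and heteroscedastic therapist models, because that choice needs the arm and cannot be made blind.
- State that the therapist-clustered, adherence, per-protocol, completer and intervention-cost analyses are done unblinded, and that the health economist is unblinded from costing onward.

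The cost is one extra data export, a dated sign-off by staff already in post, and a narrower blinding claim in the final report. Treatment, sample size and estimand are unchanged.
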